### Data analysis

All data will be collected and stored under de-identified study ID. Data will be analysed by an independent statistician. Population characteristics between the groups will be compared initially to identify any potential confounding variables. Data will be analysed on an intention to treat basis comparing primary and secondary outcomes in both groups. Analyses will make adjustment for recruiting site and thrombophilia status. *P*-value <0.05 will be considered significant.

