### Obstetric care and trial procedure (Fig. 1)

**Fig. 1 Fig1:**
[figure not shown]
Individual participant trial schedule

All women will have serum samples taken at recruitment, 20 and 30 weeks gestation. Samples will be centrifuged and stored in −80 °C freezer for later assessment of placental and angiogenic growth factors (Table 1). At the time of fetal anatomy scan, standard fetal growth parameters [43, 44] and uterine and umbilical arterial Doppler waveforms [45] will be recorded. These ultrasound measurements will be repeated at 24 weeks’ gestation. Data from any additional antenatal ultrasound scans will also be collected.

**Table 1 Tab1:** EPPI trial key secondary study outcomes

Combined	Preeclampsia and/or SGA <10th centile Preeclampsia and/or SGA <10th centile delivered <35^+6^ weeks Preeclampsia and/or SGA <10th centile delivered <33^+6^ weeks Preeclampsia and SGA <10^th^ centile delivered at any gestation
Maternal	Preeclampsia Severe preeclampsia Placental abruption Caesarean section delivery Antepartum haemorrhage Postpartum haemorrhage <500mls and <1000mls
Infant	SGA <10^th^ centile SGA <5^th^ centile SGA <3^rd^ centile Unexplained intrauterine fetal death Stillbirth Gestational age at delivery Mean birthweight Mean birthweight centile Neonatal Intensive Care Unit admission Neonatal death
Uteroplacental	Abnormal uterine artery Doppler waveform at 20 or 24 weeks Abnormal umbilical artery Doppler waveform at 20 or 24 weeks
Placental & angiogenic growth factors	soluble fms-like tyrosine kinase-1 (sFlt-1) soluble endoglin (soluble Eng) Endothelin-1 (ET-1) Placental growth factor (PLGF) soluble vascular cell adhesion molecule 1 (VCAM1)

*SGA* small for gestational age, all SGA measured by customised birthweight centile [46]

For women receiving LMWH, an educational session regarding injection technique will be provided by a research midwife prior to treatment commencement. LMWH injections will be re-supplied on a monthly basis from hospital pharmacies. Treatment will continue until 36^+0^ weeks but additional safety indications to stop treatment sooner include; need for delivery prior to 36^+0^ weeks (stop once decision made for delivery or 12 h prior to induction of labour or elective caesarean section, whichever is later), episode of threatened preterm labour (treatment can be recommenced if symptoms settle), clinical evidence of placental abruption or thrombocytopenia with platelet count <80 × 10^9^/L.

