### Study outcomes

The primary outcome is the incidence of preeclampsia and/or small for gestational age (SGA) <5^th^ customised birthweight centile [46]. Preeclampsia will be defined as new onset hypertension (systolic BP ≥140 mmHg and/or diastolic BP ≥90 mmHg) arising after 20 weeks gestation with evidence of significant proteinuria (dipstick proteinuria (≥1+) subsequently confirmed by spot urine protein/creatinine ratio ≥ 30 mg/mmol and/or 24 h urine protein excretion >0.3 g) or any multi-system complication including haematological, liver, renal and neurological involvement [47]. IUGR is difficult to define and measure and so SGA defined by customised birthweight centiles will be used as the most reproducible surrogate. Customised centiles adjusting for infant sex, gestation at delivery and maternal variables—parity, ethnicity, height and weight will be used [46]. The key secondary study outcomes are shown in Table 1.

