### Sample size

We have estimated a risk of recurrence of preeclampsia and/or SGA < 5^th^ customised centile for the included population of 25% when managed routinely with aspirin (and calcium). A trial of 160 participants, allowing for a 5% drop-out/early miscarriage rate will have 80% power at a two-sided significance level of 0.05 to detect a difference between 25 and 7% [37].

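### One p<0.05 rule covers the primary outcome and all 27 or 28 key secondary outcomes, so secondary results can be called significant without error control

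*Protocol article*

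**What the plan says.** The protocol article names one primary outcome (Study outcomes): "The primary outcome is the incidence of preeclampsia and/or small for gestational age (SGA"), with the small-size component set at the 5th customised centile. The same section adds: "The key secondary study outcomes are shown in Table 1". That table is titled "EPPI trial key secondary study outcomes", and nothing in it ranks one entry above another.

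The Data analysis section describes an intention-to-treat analysis "comparing primary and secondary outcomes in both groups", adjusted for site and thrombophilia status. It closes with the only decision rule in the article, that a P "value <0.05 will be considered significant". The rule names no tier of outcome.

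The Sample size section rests on the primary outcome alone: "A trial of 160 participants, allowing for a 5% drop-out/early miscarriage rate will have 80% power" to detect 25% against 7%.

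**The concern.** The article fixes a threshold for calling a result significant and places it directly after a sentence that covers both tiers of outcome. A secondary outcome at p=0.04 would then be significant on the same footing as the primary.

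The setting makes this matter. The trial is sized for a very large effect, and the Background reports three later trials with no benefit. A non-significant primary beside one or two nominally significant secondaries is therefore a foreseeable result. The Discussion also says in advance that outcome differences would probably be attributable to enoxaparin. Its argument there is that both arms receive the same background care, but that does not exclude chance. At stake is the reading of secondary results in the trial report and in later citations, not the validity of the primary test.

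**Working it through.** **1. The plan's own figure.** The article gives no family-wise error figure. Its only related number is the sample size for the primary outcome.
- Inputs (Sample size section): 25% vs 7%, two-sided 0.05, 80% power, 5% drop-out.
- n per arm = [1.960·√(2·0.16·0.84) + 0.842·√(0.25·0.75 + 0.07·0.93)]² / 0.18² ≈ 64. With continuity correction it is 75.
- Total 2 × 75 = 150, and 150/0.95 ≈ 158, close to the stated 160. Without the correction, 128/0.95 ≈ 135, which does not match.
- So 160 is reproduced for the primary alone. After 5% loss, 160 × 0.95 / 2 = 76 women per arm.

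**2. Power for a smaller effect (25% vs 15%, my assumption).** With 76 per arm:
- z = [0.10 − 1.96·√(2·0.20·0.80/76)] / √((0.1875 + 0.1275)/76) = (0.100 − 0.127)/0.064 ≈ −0.42.
- Power is about 34%, so a missed primary is realistic.

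**3. Count of Table 1.** 4 combined + 6 or 7 maternal + 10 infant + 2 Doppler + 5 growth factors = 27 or 28. The count turns on "Postpartum haemorrhage <500mls and <1000mls", which is one item with two thresholds.

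**4. Upper figure, independent tests of exact 5% size.**
- 1 − 0.95^27 = 0.750 and 1 − 0.95^28 = 0.762.
- Expected false positives: 27 × 0.05 = 1.35 and 28 × 0.05 = 1.4.

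**5. Correlated test statistics (simulation; correlations assumed).**

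| Structure | Chance of at least one p<0.05 |
|---|---|
| 28 tests, common correlation 0.2 | 70% |
| 28 tests, 0.3 | 64% |
| 28 tests, 0.5 | 49% |
| 28 tests, 0.7 | 33% |
| By outcome domain, 0.5 within and 0.1 between* | 66% |
| By outcome domain, 0.7 and 0.2* | 55% |
| By outcome domain, 0.8 and 0.3* | 46% |

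*29 tests including the primary. One test more or less changes little: at common correlation 0.3, 28 tests give 64% and 29 give 65%.

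These figures count results in either direction. For 28 tests, the chance of at least one result favouring enoxaparin is 51% under independence, 34% at correlation 0.3 and 25% at 0.5.

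**6. Rare outcomes.** With 76 per arm, the actual size of a nominal 5% test falls well below 5%. At an event rate of 1% it is 0.7% for an uncorrected test and 0.01% for Fisher's exact test. At 2% it is 2.9% and 0.2%. At 5% it is 4.9% and 1.5%.

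**7. Patient-level null simulation.** It used 76 per arm and 28 secondaries. The small-size categories were nested, severe preeclampsia lay within preeclampsia, and stillbirth, abruption and neonatal death were rare. Event rates were assumed, and three assumed strengths of dependence were tried. Results for the secondaries alone:
- Uncorrected tests: 54–61% with at least one p<0.05. The mean number over all 29 tests is 1.26–1.28; less about 0.05 for the primary, this leaves about 1.2.
- Continuity-corrected tests: 38–45%. The mean is 0.79–0.82; less about 0.03, this leaves about 0.8.
- The primary's own rejection rate at a single final test was about 5% uncorrected and 3% corrected. The secondaries do not alter it.

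**The case against.** The strongest reply is that this is a condensed article whose statistical analysis plan is not shown. Handling of multiplicity among secondaries commonly belongs in that plan, and P<0.05 may be no more than a conventional nominal threshold. The article also keeps a clear order of outcomes: one named primary, a table labelled secondary, and a sample size based on the primary.

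Much of this stands. The absence of a multiplicity correction is no error, and nothing in the article says that a secondary could establish efficacy. What remains is that the article is not silent. It states the rule and applies it to both tiers, so a narrower rule in the analysis plan would be qualifying the published text.

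Three stronger readings are tempting, and the document does not support them:
- **That the primary result is compromised.** With one named primary, testing secondaries does not change its type I error.
- **That a false-positive secondary is close to a three-in-four certainty.** That needs independent tests of exact 5% size. Table 1 has nested centile cut-offs, composites built from shared components, overlapping fetal death outcomes and rare events.
- **That the count should be multiplied by visits.** The article does say "All women will have serum samples taken at recruitment, 20 and 30 weeks gestation", but not that each time point is tested separately. The Doppler entries read most naturally as abnormal at either scan. A count such as 28 + 2 + 5 = 35 would rest on an assumed test plan and is not used here.

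Two objections to the remedy are also fair. A 95% confidence interval that excludes the null carries much the same information as p<0.05, so the change governs what is claimed, not how often chance differences occur. A blanket ban on significance statements would also cover bleeding outcomes of an anticoagulant and could mute a safety signal. The fix separates those outcomes for that reason.

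**Conclusion.** The point holds as a cheap improvement to a stated rule, not as a flaw in the primary analysis. One p<0.05 rule spans the primary and 27 or 28 undifferentiated secondaries. If enoxaparin does nothing, the chance of at least one nominally significant secondary is roughly 40–65%, so about even odds. The figure is 75–76% under independence and could be nearer one third with very strong correlation. The expected number of false positives is about 0.8 to 1.4. The document gives no correlations and no event rates for most secondary outcomes, so the range rests on assumptions. The conclusion does not depend on the exact value: even 40% is eight times the 5% that a reader attaches to the word significant.

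**What to change.** In the Data analysis section, replace the general threshold sentence with a rule by tier:
- The claim of statistical significance at p<0.05 is reserved for the primary outcome. Whether the interim analysis alters that final threshold is a separate question, not examined here.
- The Table 1 efficacy, Doppler and growth-factor outcomes are reported as effect estimates with 95% confidence intervals, labelled supportive or exploratory.
- Possible harms (antepartum and postpartum haemorrhage, placental abruption) are reported separately as safety outcomes, with estimates and unadjusted 95% confidence intervals.

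If an analysis plan already says this, the protocol text need only be brought into line with it. The cost is a few lines of text. The sample size stays at 160, no data are added, and the estimates remain usable for later meta-analysis. The downside is that a secondary efficacy result can no longer be called significant on its own.

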## Discussion

This is a protocol for a randomised trial to assess the role of the LMWH, enoxaparin, to prevent recurrence of preeclampsia and IUGR in women at high risk based on their past obstetric history. The EPPI trial has been designed to focus specifically on the related conditions of preeclampsia and IUGR. The inclusion criteria aim to identify women with or without thrombophilia but do not include less specific or poorly defined conditions such as past venous thromboembolism, recurrent miscarriage, unexplained fetal death and placental abruption as seen in some other trials of heparin therapy for the prevention of preeclampsia and IUGR. The pathological mechanisms of such a wide variety of conditions are likely to be significantly different from those of preeclampsia and IUGR and a single preventative therapy less likely to be effective for all. Similarly the composite primary outcome measure for this study has been limited to preeclampsia and a measure of IUGR (SGA) so results are more likely to be relevant to these placental mediated conditions.

Another strength of this study is that both treatment arms will receive standard high risk care including the use of aspirin in all women and, for those with previous history of preeclampsia, the use of calcium. Any differences observed in outcome are likely to be related to enoxaparin use.

This study will include 160 women and is one of the larger studies in this area. The findings of this trial will be available for future meta-analysis and systematic reviews. It will significantly contribute to and further current knowledge regarding the use enoxaparin in pregnancy to reduce recurrence of preeclampsia and IUGR.
